### Ethical Considerations

The trial has been approved by the local health district ethics committee (2024/PID02885 - 2024/ETH02492) and is currently screening participants for recruitment. Written informed consent will be obtained from all participants. The participants will be informed that a withdrawal of consent is possible at any point and that their clinical care will not be compromised. The participants will not receive any remuneration.

## Results

This manuscript describes the protocol for an ongoing pilot trial, with results to be reported upon trial completion. Recruitment for the trial began in August 2025. As of manuscript submission, 4 participants have been enrolled, with a target of 20 participants by the end of August 2026. Data analysis is expected to be completed by December 2026. The results are planned to be published as an open-access article in 2027 and used to inform the design of a larger trial.

A summary of the results will be disseminated to the participants.

## Discussion

### Anticipated Findings

This pilot study primarily aims to assess the feasibility of combining TENS with self-selected music. The anticipated results include approximately 80% adherence to daily use of TENS or TENS combined with self-selected music and completion of daily diaries on 80% of the study days. An adherence rate of 80% will be considered sufficient for the current data collection methods to be deemed feasible for a larger trial. It is hoped that adherence to data collection procedures, including real-time documentation of pain scores and medications used, will be evaluated among participants [15]. The trial is not likely to reveal any additive analgesic benefit for TENS and self-selected music due to the small participant numbers, but it is anticipated that a trend toward improved pain scores, better function, and reduced analgesia requirements by combining the 2 modalities may be revealed. A change of 2 points in the 11-point scale on the NRS will be most clinically relevant, but even a point difference in the NRS can be considered as the minimal clinically significant change to the participants [16]. A change in pain intensity of 2 points in the NRS is accepted as best correlated with general patient satisfaction and other meaningful outcome measures in chronic low-back pain [17]. The clinically meaningful change will differ by baseline pain; however, for pragmatic reasons in this feasibility trial, it was decided to not stratify participants based on baseline pain and adopt the general threshold. It is hoped that the acceptability of combining TENS with self-selected music as an intervention for pain management will be determined, and whether the outcome measurements and methods are perceived as burdensome and time-consuming will be assessed in this small sample. Additional insights are expected regarding noncompliance with the treatment, which may include lack of perceived improvement in pain or adverse events associated with use, such as worsening pain or skin irritation from the electrodes, as well as other factors such as lack of motivation [18].

Chronic pain is a complex condition, and the intensity of pain and the functional limitations experienced by people with chronic pain are best managed using a biopsychosocial framework [19]. The use of TENS and self-selected music will fit within this framework, along with education and an interdisciplinary pain self-management program, to achieve person-centered functional goals by addressing the multiple contributors to a person’s pain experience [20]. The 2-week time frame for the intervention, rather than an in-clinic comparison, will provide a more pragmatic approach to test the real-world efficacy of combining the interventions [21]. Focusing not only on improvement of pain scores but also on other aspects of pain management, including mood, function, and medication use, will provide a comprehensive picture of the interaction between the 2 modalities.

The self-selection of the pulse amplitude, frequency, and mode is recommended due to the complexity of the pain experience. TENS provides optimal analgesia when the delivered sensation is comfortable for the person experiencing pain [22]. Self-selection of the TENS parameters and music also has the potential to increase the sense of control of the participants, thus improving self-efficacy, which can also reduce pain intensity and improve compliance [23]. Due to constraints related to resources and time, a smaller number of participants were selected, as this is a feasibility trial. A crossover trial design was chosen where participants were their own controls to reduce the sample size [24]. We chose not to have a washout period due to the short-acting nature of the intervention, with evidence that postuse analgesia usually wears off by 24 hours for TENS [22].

The duration of analgesia from music listening interventions in chronic pain is unclear, but available evidence indicates that it is short-lived and does not last hours or days beyond the session [25]. The clinical trials using TENS do not consistently report adherence rates and can vary from 50% to 80% [18]. We chose the higher adherence rate, as this is a feasibility study. Those with previous exposure to TENS or music listening interventions were excluded due to the potential for placebo effects arising from previous experience [26]. Stratification of participants based on their previous use of TENS or music listening interventions could have reduced this bias in recruitment. However, given the small sample size and the pilot feasibility nature of this study, stratification would have introduced unnecessary complexity and was not aligned with the primary objective, which was to assess the feasibility of data collection methods [27].

### Limitations

The study requires the participants to fill out a significant amount of information daily, which may contribute to participant burden. It also increases the risk of noncompliance with regular entries and introduces recall bias if participants try to record the information before review. One of the main limitations of the study will be the lack of concurrent electronic monitoring to complement the participant-reported data. The study methodology also does not allow for blinding of the participants due to the crossover design. We have excluded participants who cannot communicate in English, those who cannot use the TENS machine due to functional limitations, and those who are unable to use streaming technology or other technology that plays music for pragmatic reasons in this feasibility trial. The research team acknowledges that this will affect the generalizability of the results by excluding culturally diverse cohorts and those who are less tech savvy. However, such individuals are expected to represent only a small proportion of otherwise eligible participants. This point will be addressed if a larger trial is considered feasible. Participants have considerable flexibility in choosing the frequency, mode, and electrode placement when using TENS, as well as the type of music they listen to. While this variability makes it challenging to determine which parameters were truly effective, predict underlying mechanisms, and replicate results, these limitations are acknowledged. As this study primarily focuses on feasibility, such factors will be carefully addressed when designing a larger trial. The pilot study is designed to detect only large effect sizes and to inform power calculations for future trials, and it may fail to detect small effect sizes. It is anticipated that approximately 90% of participants will need to demonstrate a positive trend, defined as at least a 1-point improvement on the NRS, with the combination of TENS and self-selected music, to calculate the participant numbers for a larger trial that is adequately powered to detect a moderate effect size [28]. However, the authors anticipate that the effect sizes and the CIs from the pilot study will help to calculate a conservative estimate to detect smaller effect sizes from a larger definitive trial [29].

### Future Directions

If the trial is feasible and indicates a positive synergistic trend with TENS and self-selected music, it will help to plan for a larger trial with more varied pain diagnoses, including acute and chronic pain other than spinal pain. The aim of a larger study will be to show if combining the 2 modalities of music and TENS will improve pain intensity and function more than TENS alone. The pilot will test the feasibility of using pain diaries as a reliable indicator of gathering information in a larger trial. Future directions could include automated methods for data collection, which could provide more reliable indicators of adherence, function, and medication use.

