**Conclusions:**

If the pilot trial is feasible and indicates a positive synergistic trend with TENS and music, the trial will help to inform the feasibility for a larger trial with more varied pain diagnoses, including acute and chronic pain.

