### Aims

The primary aim of this study is to test the feasibility of a clinical trial comparing TENS alone to TENS combined with listening to self-selected music in participants with low-back pain with or without leg pain lasting more than 3 months. The results of this feasibility study will be used to inform a larger trial of these interventions in participants with persistent neck and low-back pain lasting more than 3 months. A larger study will be considered feasible if 80% or more of the eligible population consents to the study and 80% or more of the participants are able to adhere to the protocol. The secondary aims are to explore if combining the 2 modalities has a synergistic effect on analgesia and function. A difference of 2 points in the numerical rating scale for pain intensity will be considered significant.

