### Power Calculation

Power was planned for the primary within-subject comparison (paired difference between TENS with self-selected music and TENS), with a 2-sided *α*=.05 and 80% power. In the absence of previous variance data, sensitivity analyses were conducted across standardized paired effect sizes (dz). The required numbers of completed pairs (participants who complete both study periods) are presented in Table 2.

**Table 2. T2:** Sample size calculation.

Effect size (dz)	Completed pairs needed, n	Recruits with 10% dropout, n	Recruits with 20% dropouts, n	Recruits with 30% dropouts, n
0.4	52	57	62	68
0.5	34	37	41	44
0.6	24	26	29	31
0.7	19	21	23	25
0.8	15	17	18	20

As a pilot study (target recruitment N=20), the trial is adequately powered only for larger effects (approximately dz≥0.70). Therefore, the primary purpose of this pilot study is to assess the feasibility, estimate variance, and provide effect size estimates to inform the definitive sample size for the main trial.

All calculations were performed using G*Power version 3.1 (Heinrich Heine University), which is widely used for sample size and power analysis in clinical research.

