### Statistical Methods

This study is a 2-period, 2-sequence crossover pilot trial without a washout period between treatments. Analyses will primarily focus on feasibility outcomes (recruitment, adherence, data completeness, and dropout) using descriptive statistics (means, medians, and proportions) with 95% CIs rather than formal hypothesis testing. These feasibility metrics will inform the practicality of conducting a larger definitive trial.

For the primary clinical outcome of pain intensity, exploratory analyses will first be conducted using paired *t* tests to compare mean scores between TENS and TENS with self-selected music within participants. Normality of paired differences will be assessed using graphical methods and the Shapiro-Wilk test. If assumptions are violated, the Wilcoxon signed-rank test will be applied as a nonparametric alternative. Categorical variables (eg, adverse events and compliance categories) will be analyzed initially using chi-square tests, or Fisher exact test if expected cell counts are small. All tests will be 2-sided with a significance level of *α*=.05.

Following these preliminary analyses, formal modeling tailored to the crossover design will be undertaken. Linear mixed-effects models will be specified with fixed effects for treatment (TENS vs TENS with self-selected music), period, and sequence, and a random intercept for participant to account for within-participant correlations. Because no washout period is present, carryover effects will be explicitly assessed by including a prior-treatment term and by examining period×sequence interactions. If evidence of carryover is observed, analyses will be restricted to first-period data as a sensitivity check, treating it as a parallel-group comparison.

Secondary outcomes (mood, function, satisfaction, medication use, and adverse events) will be analyzed using appropriate mixed-effects regression models: linear for continuous outcomes, cumulative logit for ordinal outcomes, negative binomial for counts, and logistic for binary outcomes. These analyses are exploratory in nature. Given the pilot design and small sample size, no formal correction for multiple testing will be applied; instead, effect sizes and CIs will be reported to guide future sample size calculations.

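### The conditions for moving to a larger trial disagree across the article, and they include an efficacy trend that a 20-person pilot cannot support as a criterion

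*Protocol article*

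**What the plan says.** Four parts of the protocol article bear on whether and how a larger trial follows.

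- **Introduction, Aims:** "A larger study will be considered feasible if 80% or more of the eligible population consents to the study", and if at least 80% of participants can adhere to the protocol. There is no efficacy element.
- **Abstract, Conclusions:** "If the pilot trial is feasible and indicates a positive synergistic trend with TENS and music", the pilot will help inform a larger trial. **Discussion, Future Directions** repeats this: "If the trial is feasible and indicates a positive synergistic trend with TENS and self-selected music, it will help to plan for a larger trial". Neither place gives a threshold, an outcome or a comparator for the trend.
- **Discussion, Limitations:** "approximately 90% of participants will need to demonstrate a positive trend, defined as at least a 1-point improvement on the NRS". This is tied to calculating participant numbers for the larger trial. It is the only definition of a positive trend in the article, and it does not say whether improvement is counted against TENS alone or against baseline.
- **Discussion, Anticipated Findings:** the pilot is not expected to show an additive analgesic benefit because it is small, but "a trend toward improved pain scores, better function, and reduced analgesia requirements by combining the 2 modalities may be revealed".

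Power Calculation states the limit of the design: "As a pilot study (target recruitment N=20), the trial is adequately powered only for larger effects (approximately dz≥0.70"). Statistical Methods calls the clinical analyses exploratory and plans to report effect sizes with CIs.

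**The concern.** If feasibility is met but the pain estimate is unfavourable, the Aims criteria are satisfied while the condition in the abstract and Future Directions is not. If feasibility is met and the estimate is favourable, but fewer than about 90% of participants improve by 1 point, Limitations implies that the larger trial cannot be sized as intended. The article does not say which statement governs, so the choice could be made after the data are seen.

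The added element also asks the pilot for an efficacy signal that the article itself says 20 participants are unlikely to give. A trend could be cited in support of the next trial while carrying little information. Conversely, a feasible and useful combination could be set back by the sign of a small-sample estimate or by a responder count that is almost unreachable.

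**Working it through.** **Inputs from the article.** Target N = 20, with each participant as own control; two-sided α = 0.05; 80% power; a 1-point NRS improvement in about 90% of participants (Limitations); a 2-point NRS difference treated as significant (Aims).

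**Assumptions, because the article gives no figure.** SD of the paired NRS differences 1.5 to 3 points; a small true benefit of dz = 0.2, with 0.1 to 0.5 as the range, where dz is the mean paired difference divided by its SD; normally distributed differences; 20 completers unless stated.

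**Step 1. Reproduce the plan's figure.** The smallest n giving 80% power for a paired t test (noncentral t) is 52, 34, 24, 19 and 15 for dz = 0.4, 0.5, 0.6, 0.7 and 0.8. These match the completed pairs in Table 2. With 20 completers, power at dz = 0.70 is 84% and the effect detectable at 80% power is dz = 0.66. The statement that the pilot can detect only large effects is correct.

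**Step 2. Reading A: a trend is a mean pain difference in favour of music.** P(favourable) = Φ(dz × √n), with √20 = 4.472.

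| True dz | dz × √20 | Met | Missed |
|---|---|---|---|
| 0 | 0 | 50.0% | not applicable |
| 0.1 | 0.447 | 67.3% | 32.7% |
| 0.2 | 0.894 | 81.4% | 18.6% |
| 0.3 | 1.342 | 91.0% | 9.0% |
| 0.5 | 2.236 | 98.7% | 1.3% |

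With 16 completers and dz = 0.2, dz × √n = 0.2 × 4 = 0.8, and the trend is missed 21.2% of the time.

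If pain, function and analgesic use are all considered, the null probability depends on how they are combined. For three equicorrelated normal estimates, P(all favourable) = 1/8 + (3/4π) × arcsin(r), and P(at least one) = 1 minus the same quantity. For r from 0 to 0.7, all three are favourable 13% to 31% of the time, and at least one is favourable 88% down to 69% of the time.

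**Step 3. Reading B: the Limitations definition, compared with TENS alone.** 90% of 20 is 18. P(met) = P(X ≥ 18) for X ~ Binomial(20, p), where p is the true share improving by at least 1 point.

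- No effect: for differences symmetric about zero, p cannot exceed 0.5. At p = 0.5, P = (190 + 20 + 1)/2^20 = 211/1,048,576 = 0.02%. This is an upper bound.
- True 2-point mean benefit: p = Φ((2 − 1)/SD).

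| SD of differences | p | P(at least 18 of 20) |
|---|---|---|
| 1.5 | 0.748 | 8.7% |
| 2 | 0.691 | 3.0% |
| 2.5 | 0.655 | 1.4% |
| 3 | 0.631 | 0.8% |

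At SD = 3, a 2-point benefit is dz = 2/3 = 0.67, just above the 0.66 that 20 completers detect with 80% power. The responder rule would therefore be met 0.8% of the time where the paired t test succeeds about 80% of the time. Even if the true responder share were 90%, the rule would be met only 67.7% of the time.

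**Step 4. Reading C: the Limitations definition, compared with baseline.** Improvement produced by TENS itself then counts. The share improving is no longer capped at one half when music adds nothing, so the count does not isolate the contribution of music. No probability can be given, because the article states no expected response to TENS.

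**The case against.** A reader might infer that the article sets a formal go/no-go rule that is met at least half the time when music adds nothing and fails about one time in five when music has a small benefit. The documents do not support that.

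- No section states a bare sign rule. The only definition of a positive trend is the one in Limitations, and under it the error pattern reverses: almost never met under no effect, and almost never met under a real one.
- One half is exact for a single outcome. It is exceeded only if any one of several outcomes may count. Anticipated Findings joins its three outcomes with a conjunction, and it describes a hope rather than a criterion.
- One in five depends on dz = 0.2, which the article does not state.
- Saying that results will help to plan or inform is softer than a stopping rule. Nothing says the larger trial would be abandoned without a trend.

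The authors could add that Aims describes a larger trial in neck and low-back pain, while the abstract and Future Directions describe wider diagnoses including acute pain, so two different successors may be meant. They could also say that the limited power is openly acknowledged.

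The first four points stand, and they limit how the percentages may be used. The fifth is possible, but the article does not draw the distinction. Acknowledging low power does not resolve it either: it makes an efficacy condition harder to justify. None of these points reconciles the four statements.

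**Conclusion.** The point holds as an inconsistency with a statistical consequence. Aims rests progression on feasibility; the abstract and Future Directions add an undefined trend; Limitations attaches a 90% responder requirement to sizing the next trial. Depending on the reading, the efficacy element is a coin flip under no effect (50%, with 1% to 33% missed for dz from 0.5 down to 0.1), a bar met only 0.8% to 8.7% of the time with a true 2-point benefit, or a count that mixes in the effect of TENS. No reading gives a usable criterion.

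The percentages are conditional on the stated reading, on 20 completers, on normal differences, and on an SD of 1.5 to 3 and dz values that are assumptions. They describe what each reading would do, not a rule the authors have adopted. The feasibility criteria and the pair numbers in Table 2 are not affected.

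**What to change.** Remove the trend clause from the abstract's Conclusions and from Future Directions, and remove the 90% requirement from Limitations, so that progression rests on the consent and adherence criteria in Aims. Changing only the first two would leave the responder requirement standing. Report the estimated difference between TENS with music and TENS alone with its 95% CI; effect sizes and CIs are already planned.

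If an efficacy check is wanted, a sentence such as this would do: *Pain data will argue against proceeding only if the 95% CI for the benefit of TENS with music over TENS alone excludes the prespecified clinically relevant benefit; a favourable point estimate alone is not a criterion.* One value must be fixed in advance, because Aims uses 2 points and Anticipated Findings mentions both 1 and 2. The choice matters: with 20 completers the CI half-width is about 2.093 × SD/√20, which is 0.70 points at SD 1.5 and 1.40 at SD 3. An observed difference of zero would exclude a 2-point benefit at either SD, but would exclude a 1-point benefit only at the smaller SD.

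The cost is a few clauses in three places, with no new data or analysis. The downside is that the authors can no longer cite a trend as support for the next trial.
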